## Abstract

**Introduction:**

Heavy drinkers in contact with alcohol services do not routinely have access to testing to establish the severity of potential liver disease. Transient elastography by FibroScan can provide this information. A recent systematic review suggested providing feedback to patients based on markers of liver injury can be an effective way to reduce harmful alcohol intake. This randomised control trial (RCT) aims to establish the feasibility of conducting a larger national trial to test the effectiveness of FibroScan advice and Alcohol Recovery Video Stories (ARVS) in changing high-risk drinking behaviour in community alcohol services common to UK practice.

**Methods and analysis:**

This feasibility trial consists of three work packages (WP). *WP1*: To draft a standardised script for FibroScan operators to deliver liver disease-specific advice to eligible participants having FibroScan. *WP2*: To create a video library of ARVS for use in the feasibility RCT (WP3). *WP3*: To test the feasibility of the trial design, including the FibroScan script and video stories developed in WP1 and WP2 in a one-to-one individual randomised trial in community alcohol services. Semi-structured interviews will be conducted at 6 months follow-up for qualitative evaluation. Outcomes will be measures of the feasibility of conducting a larger RCT. These outcomes will relate to: participant recruitment and follow-up, intervention delivery, including the use of the Knowledge of LIver Fibrosis Affects Drinking trial FibroScan scripts and videos, clinical outcomes, and the acceptability and experience of the intervention and trial-related procedures. Data analysis will primarily be descriptive to address the feasibility aims of the trial. All proposed analyses will be documented in a Statistical Analysis Plan.

**Ethics and dissemination:**

This trial received favourable ethical approval from the West of Scotland Research Ethics Service (WoSRES) on 20 January 2021, REC reference: 20/WS/0179. Results will be submitted for publication to a peer-reviewed journal.

**Trial registration number:**

ISRCTN16922410.

Strengths and limitations of this studyThe Knowledge of LIver Fibrosis Affects Drinking (KLIFAD) trial is the first randomised control trial to evaluate the feasibility of using non-invasive liver stiffness measurement and alcohol recovery video stories as a behavioural intervention.The mixed-methods design of the KLIFAD trial will enable us to test the acceptability of trial-specific procedures to participants and key alcohol workers.The KLIFAD trial will enable a definitive trial to establish the effectiveness of non-invasive screening for liver fibrosis in community alcohol services.The primary limitation of the KLIFAD trial is that it is a single-centre trial which could limit the generalisation of findings.Due to the nature of the KLIFAD intervention, blinding is not possible.

## Introduction

Alcohol-related liver disease (ARLD) is the most common cause of cirrhosis in the UK, and mortality from ARLD has risen significantly over the past three decades. It is now the second most common cause of working life years lost in men and fifth in women.^1 2^ Europe has one of the highest prevalence of Alcohol Use Disorders (AUD), involving 15% of men and 3.5% of women.^2^ Around 25% of the UK population drink above the UK recommended level of 14 units per week, and 10% are harmful drinkers.^3^ The UK’s total per capita pure alcohol intake for people age ≥15 years is 11.4 L/annum per person, which is twice the global average of 6.4 L/annum per person.^2 3^ Approximately 20%–30% of lifelong drinkers develop liver cirrhosis, and the risk is even higher (35%) among harmful drinkers.^4 5^

ARLD causes no symptoms in its earlier stages; indeed, patients are often unaware they have serious physical health problems until they present with the complications of cirrhosis, for example; ascites, jaundice, encephalopathy, variceal bleed and liver failure, when the opportunity for treatment and recovery of liver health is significantly reduced.^1 5 6^ It is estimated that the cost to the UK of alcohol on health is £3.5 billion per year,^3 7^ consuming 3.6% of the National Health Service (NHS) annual budget.^8^ In England, there were 5698 alcohol-specific deaths in 2018, the alcohol-specific age-standardised death rate was 11.9/100 000 (male=16.4 female=7.6). Nottingham (UK) has one of the highest (total=18.6, male=26.8 and female 10.2) alcohol-specific age-standardised death rate/100 000 in the country.^9^ A recent trial from the USA predicted a 75% increase in age-standardised annual mortality and a 65% increase in decompensated cirrhosis due to ARLD over the next two decades.^10^

Systematic reviews of randomised controlled trials (RCTs) have established that delivering brief advice about alcohol to harmful drinkers helps them reduce their alcohol consumption.^11 12^ Most studies were conducted in primary care settings where the prevalence of liver disease is likely to be markedly lower than in specialist alcohol treatment services. In alcohol services, where high levels of physical and psychological dependence on alcohol are frequent, National Institute of Clinical Excellence guidelines state adults with high levels of alcohol dependency should be assessed and offered intensive structured community-based interventions (with or without medical therapy) as these provide the best chance of achieving and maintaining abstinence from alcohol.^13^ Most clinical services in the UK are based on these principles. Individual programmes vary by locality with many of these services delivered by non-NHS providers. Despite the delivery of brief advice and other alcohol-related interventions in clinical practice for over two decades, mortality and morbidity due to alcohol misuse continues to rise in the UK.^3^ There is a pressing need to optimise existing interventions to reduce harmful alcohol intake and examine effective alternative options.

Early diagnosis of liver fibrosis provides an opportunity to intervene and reduce or stop alcohol intake. This is known to be the most effective way of preventing liver disease progression.^14^ Transient elastography by FibroScan (Echosens, France) has been used in primary care (General Practice) settings to detect liver disease in populations identified as having liver disease risk (heavy drinkers and those with type 2 diabetes). These studies showed that screening asymptomatic individuals based on risk for liver disease doubles the rates of liver cirrhosis diagnosis in the primary care populations studied.^15 16^ Moreover, a recent systematic review suggested providing feedback to patients based on markers of liver injury can be an effective way to reduce harmful alcohol intake.^17^ Access to recovery stories can help address mental health problems and support recovery from addiction.^18 19^ Peer support from people who have recovered from alcohol misuse is beneficial in modifying high risk drinking behaviour.^20^

This trial aims to investigate the feasibility and acceptability of conducting an RCT in community specialist alcohol services settings run by Nottingham Recovery Network (NRN) and to test the acceptability of trial interventions (FibroScan and Alcohol Recovery Video Stories, ARVS).

### Selection of the term ‘alcohol misuse’

We acknowledge the heterogeneity in language used to describe alcohol use, and also the stigma associated with some commonly used terms, which itself can act as barrier to change.^21^ Some terms, such as alcohol use Disorder (AUD), are not well understood in the general population. The concept for this feasibility trial was developed in collaboration with Patient and Public Involvement (PPI) groups. After extensive discussion between the study team and PPI groups, we have opted for the term ‘alcohol misuse’ as a general term to cover excess alcohol intake, harmful alcohol intake, drinking problems, alcohol dependence, and AUD.

We define alcohol misuse as ‘weekly alcohol intake ≥14 units, or an Alcohol Use Disorder Identification Test (AUDIT) score of ≥8, or key alcohol worker and/or physician diagnosis or referral from any other services with problem drinking’.

The other definitions relevant to Knowledge of LIver Fibrosis Affects Drinking (KLIFAD) trial are provided in online supplemental material 1 (SP-Definitions).

10.1136/bmjopen-2021-054954.supp1Supplementary data

## Methods and analysis

KLIFAD is a parallel design feasibility RCT. The trial will be conducted in a single centre in the UK, carried out at three community alcohol services in Nottingham (the Wellbeing Hub, Edwin House and the Primary Care Alcohol Clinic run by the NRN) hosted by Framework and NRN and working in partnership with Nottinghamshire NHS Foundation Trust.

The KLIFAD trial consists of three work packages (WP) (figure 1).

**Figure 1 F1:**
[figure not shown]
The KLIFAD trial timeline and flow chart. The trial has three work packages (WP), WP3 is in randomised feasibility trial. AUDIT, Alcohol Use Disorder Identification Test; GCP, good clinical practice; KLIFAD, Knowledge of LIver Fibrosis Affects Drinking; RCT, randomised control trial; SADQ, Severity of Alcohol Dependence Questionnaire.

### Work package one (WP1)

WP1 aims to design a standardised script framework for FibroScan operators to deliver liver disease-specific advice to participants having FibroScan as part of the feasibility RCT (WP3).

FibroScan, is an ultrasound technology developed by Echosence, France, which non-invasively asseses liver stiffness. A prototype script for FibroScan has been created in consultation with the existing KLIFAD PPI group covering three ranges of FibroScan scores, normal ≤7 Kilopascal (kPa), intermediate fibrosis 8–15 kPa and advance fibrosis ≥15 kPa. online supplemental material 1 The trial flow chart for WP1 is provided in figure 2.

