**Figure 2 F2:**
[figure not shown]
Flow diagram for; work package one to create FibroScan scripted feedback and work package two to create alcohol recovery videos stories. KLIFAD, Knowledge of LIver Fibrosis Affects Drinking; NEON, narrative experiences online; PPI, patient and public involvement; WP1, work package one.

We will organise separate participant and FibroScan operator focus groups to collect feedback on the prototype scripts. The participant focus group will allow us to investigate the key messages to be included in the script and feedback, as well as considering how best to present the FibroScan results (eg, graphically, in the text). The FibroScan operator focus group will specifically discuss implementation in clinical practice. In addition, to evaluate the stage of change that each participant has reached, a validated readiness to change model will be piloted.^22^

Following Krueger’s (1988) focus group guide, each focus group will include five to eight participants and will last for a maximum of 2 hours.^23^ Depending on the latest COVID-19 guidelines, the focus group will be either virtual or face-to-face. A topic guide will be used (SP-Focus Group Guide WP1 V.2.0). We aim to arrange two participant focus groups and one FibroScan operator focus group. The focus groups will be facilitated by two members of the research team. Examples of questions include: (a) If you were a participant in the trial, would the script make sense to you? (b) Are there any parts of the script that you do not understand, and if so, why? (c) What is the best way to present the results of the FibroScan (eg, graphically, in the text)?

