Eligible participants (table 1) will be identified and recruited through multiple channels. For example, via existing patient forums at all three recruitment settings, the KLIFAD PPI group, by offering information to patients self-presenting to any of the trial treatment settings, snowball methods and via Black, Asian and minority ethnicity/Framework PPI groups. The focus group meeting will be recorded and transcribed verbatim either by automated software or an independent sponsor-approved transcriber. After the first participant focus group, the FibroScan script will be edited considering feedback and a second focus group will then be held to review iterated scripts. The final scripts will be sent via email to participants of focus groups for any final thoughts. We will then organise a FibroScan operator focus group of key alcohol workers working at any of the recruitment settings who are willing to give informed consent, to discuss any specific implementation issues.

**Table 1 T1:** KLIFAD trial eligibility criteria

Inclusion criteria	Exclusion criteria
Work package one	
A person age ≥18 years	Other primary substance misuse even where alcohol is a factor
Primary problem of alcohol misuse‡	Lacks capacity to confirm consent
Had FibroScan in past	
Work package two	
A person age ≥18 years	Lacks capacity to confirm consent
Primary problem of alcohol misuse	
Had FibroScan in past	
A person with lived experience of alcohol problems	
A person willing to consent to the recording and public use of their video recording	
Work package three: the randomisation phase	
A person age ≥18 years	Other primary substance misuse even where alcohol is a factor
Primary problem of alcohol misuse	Lacks capacity to confirm consent
	Referrals from driving offences and student referrals*
	Out of area clients at Edwin House†
	Participants unable to comply with trial procedures

*As these individuals are essentially not self-presenting, may have different motivation and have lower overall levels of alcohol use and so are substantially lower risk of having liver disease.

†In whom we cannot obtain follow-up data due to lack of follow-up availability.

‡Alcohol misuse was defined as, weekly alcohol intake ≥14 units, or an AUDIT score of ≥ 8, or key alcohol worker and/or physician diagnosis or referral from any other services with problem drinking.

AUDIT, Alcohol Use Disorder Identification Test; KLIFAD, Knowledge of LIver Fibrosis Affects Drinking.

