### Control group

Participants randomised to the control arm will continue with standard treatment (usual care) provided at the three treatment settings. The participants in this arm will be offered FibroScan at 6 months.

As part of standard treatment, the recruitment settings provide different types of interventions to participants in line with the National Drug Treatment Monitoring System Data set (NDTMS) and Public Health England (PHE) guidelines.^30^ Existing treatment programmes can run for up to 12 weeks.

For adult drug and alcohol services, there are three main categories of standard intervention (usual care) delivered by the NRN: (a) Psychological: which includes motivational interventions, family and social network interventions and cognitive and behavioural-based relapse prevention interventions (substance misuse specific). (b) Recovery support: which includes 12-step work and counselling.

(c) Pharmacological: which involves prescribing medication for drug and/or alcohol relapse prevention support. For example, naltrexone, acamprosate, disulfiram as part of alcohol or opioid relapse prevention therapy and Chlordiazepoxide for acute alcohol withdrawal.

Specific treatment programmes are started after an initial assessment and based on the participant’s needs. The duration of contact with services varies, most participants stay with services for 12 weeks, some get discharged early and a few stay longer than 6 months.

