#### Schedule of visits

##### Baseline

The baseline visit will be on the day when the participant starts standard treatment at any recruitment setting. At this visit, written informed consent will be given by participants and participants will be randomised to the intervention or control group. Participants in both arms will have an initial detailed assessment (SP-NRN assessment form online supplemental material 2) as part of their standard care. This includes the collection of baseline demographic and clinical data (eg, age, gender, ethnicity). Participants randomised to the control arm will continue with usual care, while participants randomised to the intervention arm will have the usual care and FibroScan followed by standardised script feedback with ARVS watched immediately after the FibroScan result.

10.1136/bmjopen-2021-054954.supp2Supplementary data

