#### Participant safety

There is a risk that being given a normal FibroScan result may provide false reassurance and encourage participants to maintain their current level of harmful drinking or encourage them to drink more. It is also possible that a high reading will generate anxiety. The trial is designed to minimise these risks by providing scripted feedback (WP1) and watching ARVS (WP2).

Cirrhosis diagnosis and FibroScan: It is anticipated that a small number of people will be identified who have previously unknown cirrhosis and so would be at risk of complications of liver disease. This will be mitigated by offering onward referral to out-patient Hepatology for all participants with a FibroScan reading >15 kPa. This will be via contact with the participant’s GP and would follow the current NUHT Nottinghamshire adult liver disease stratification pathway for referral.^39^ Some risk mitigations will be through the feedback included in this trial which covers cirrhosis.

For WP1 and WP2, we cannot foresee any potential risks except possible emotional distress during participation in a focus group or semi-structured interview. Participants can choose to skip any question that they prefer not to answer. If distress occurs during the WP3 trial visit, we will ask the participant to take a break to recover, or they can choose to terminate the process. We do not expect that the trial will cause any discomfort or pose any disadvantages, however, contact details for the trial team are provided should the participant have any questions before, during or after taking part. We have also provided a list of locally relevant support services at the end of each patient information sheet, which participants can consult.

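### A reading of exactly 15 kPa falls in two FibroScan script bands, and the hepatology referral rule disagrees with the advanced band at that value

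*Protocol article*

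**What the plan says.** Under Work package one (WP1), the protocol article describes a prototype script "covering three ranges of FibroScan scores, normal ≤7 Kilopascal (kPa), intermediate fibrosis 8–15 kPa and advance fibrosis ≥15 kPa". The sentence is followed by a pointer to online supplemental material 1.

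Under Participant safety, the measure against previously unknown cirrhosis is "offering onward referral to out-patient Hepatology for all participants with a FibroScan reading >15 kPa". It is arranged through the GP and follows a local liver disease pathway that the article cites.

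The script is not final. Once an initial group of participants has commented, "the FibroScan script will be edited considering feedback and a second focus group will then be held to review iterated scripts". For the operators, "The FibroScan operator focus group will specifically discuss implementation in clinical practice".

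In WP3 the intervention arm has "FibroScan followed by standardised script feedback with ARVS watched immediately after the FibroScan result" (Schedule of visits, Baseline). For the control arm, "The participants in this arm will be offered FibroScan at 6 months" (Control group).

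**The concern.** The band decides which feedback a participant hears straight after the scan, and WP1 exists to make that feedback standard. A rule that gives two answers for one reading works against this: on the printed wording, one operator could give the intermediate script and another the advanced script for the same 15 kPa.

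The same number also triggers a safety step, but with a different inequality. The Participant safety section relies on scripted feedback to limit false reassurance and anxiety, and on referral to deal with undiagnosed cirrhosis. At 15 kPa a participant could be given the advanced message while falling outside the stated referral offer. The offer covers all participants, and controls are offered a scan at 6 months, so the question can arise in both arms.

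**Working it through.** No sample size or power figure is involved. The check codes the printed limits as conditions on a reading x in kPa.

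**Inputs**

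- Normal: x ≤ 7 (WP1)
- Intermediate: 8 ≤ x ≤ 15 (WP1, both ends included as printed)
- Advanced: x ≥ 15 (WP1)
- Referral offer: x > 15 (Participant safety)

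**Printed rules around the cut-points**

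| Reading (kPa) | Script band(s) | Referral offer |
|---|---|---|
| 7 | normal | no |
| 8 | intermediate | no |
| 14.9 | intermediate | no |
| 15 | intermediate and advanced | no |
| 15.1 | advanced | yes |

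**Extent of the conflict**

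- Values in two bands: {8 ≤ x ≤ 15} ∩ {x ≥ 15} = {15}.
- Values labelled advanced without a referral offer: {x ≥ 15} minus {x > 15} = {15}.

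Both conflicts sit at 15 and nowhere else.

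**Possible repairs, evaluated at x = 15**

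| Change | Band(s) at 15 | Referral at 15 | Conflict left |
|---|---|---|---|
| (a) advanced to > 15 | intermediate | no | none |
| (b) intermediate to 8 ≤ x < 15, referral to ≥ 15 | advanced | yes | none |
| (c) intermediate to 8 ≤ x < 15 only | advanced | no | advanced without referral |
| (d) referral to ≥ 15 only | intermediate and advanced | yes | two bands |

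Repairs (a) and (b) clear both conflicts; (c) and (d) each leave one. Only (a) does it with a single sign.

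**Dependence on reporting precision**

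The article does not say whether readings are kept to a decimal place or rounded, so both cases are assumptions.

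- *Decimals kept:* the conflict at 15 applies to 15.0 only, but readings above 7 and below 8 (for example 7.1, 7.5 and 7.9) meet no band condition.
- *Rounded to whole kPa:* the gap between 7 and 8 disappears, but the conflict covers every reading that rounds to 15. With ordinary rounding that is 14.5 up to just under 15.5.

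**The case against.** The strongest reply is that the sentence describes a prototype in a condensed article. Operators in WP3 will work from final scripts that have been through two participant focus groups and an operator focus group. The article also points to a supplement that is not shown. Any of these may fix the limits. This stands as a limit on the claim: what is shown is a contradiction in the printed text, not in the scripts eventually used. It does not remove the point. The example questions listed for the focus groups ask whether the script is understood and how to present results; none concerns cut-points. The operator group is to discuss implementation, which might bring the limits up. The referral rule sits in the safety section, outside the script being edited.

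A second reply is that a script band and a referral threshold serve different purposes and need not coincide. Referral follows a local pathway that is not shown, and the article guarantees an offer above 15 without barring one at 15. This is fair, and it makes the referral mismatch weaker than the overlap. It also favours repair (a), which leaves the referral rule as it is. But if the two rules were meant to differ at 15, the article does not say so, and the overlap between the bands remains in any case.

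The gap between 7 and 8 kPa depends on unstated precision. It is secondary, and the finding does not rest on it.

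**Conclusion.** The point holds as a minor inconsistency in the printed text. A reading of 15 kPa meets two script bands, and it can be labelled advanced without meeting the stated referral rule. Nothing else in the article settles which applies.

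The size is one value if decimals are kept, or the readings that round to 15 if they are not. The article gives no distribution of readings, so no count of participants can be attached to it. It affects which feedback is delivered and whether the referral offer applies. It does not touch any planned summary, feasibility outcome, eligibility criterion or the target of 120.

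The conclusion rests on reading the printed intermediate range as including both ends, which is its ordinary meaning. It remains open to correction by the supplement or the final scripts.

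**What to change.** Before WP3 opens, make the three bands contiguous and non-overlapping, and use the same inequality at 15 kPa for the advanced script and the referral offer. Either of these works:

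- **(a)** Intermediate 8 to 15, advanced > 15, referral > 15. This changes one sign and leaves the referral rule untouched.
- **(b)** Intermediate 8 to < 15, advanced ≥ 15, referral ≥ 15. This changes two limits, and the new referral limit would have to be checked against the local pathway.

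In either case, state how readings are recorded. If decimals are kept, writing normal as < 8 closes the gap between 7 and 8. These wordings are examples; the choice of cut-points belongs to the clinical team.

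If the supplement or final scripts already give clear limits, the article's wording only needs to be brought into line with them. The cost is a wording change in the script and, if needed, the safety section, made during the WP1 editing already planned. It adds no patients or procedures.
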